### Study population

Eligibility criteria are described in Table 1. The IPRICE study will focus on adult patients diagnosed with R/M HNSCC considered incurable by local therapies and those eligible for treatment with pembrolizumab alone or nivolumab according to the European Marketing Authorization and managed at the Cancer Institute of Strasbourg (ICANS) Europe (Strasbourg). The patients will be enrolled in the study after screening based on the below mentioned criteria. An identification number will be assigned to each patient to be used throughout the study.

**Table 1 Tab1:**
[figure not shown]
IPRICE study inclusion and exclusion criteria

### Study assessment

Clinicians will inform all the patients enrolled in the study that their biological samples could be used for research purposes and will obtain informed consent from the participants. All participating donors may object at any time, leading to the disposal of their tissues and any derived material, as well as the cessation of data collection. The enrollment period of the study will be 3 years; each patient will be monitored for 3 years and study duration will be 6 years.

### Sample processing

#### Collection of tumor samples and liquid biopsies

Prior to first-line immunotherapy, tumor biopsy will be performed as part of standard care for patients with histologically proven disease. Tumor biopsies will be performed prior to second-line immunotherapy following chemotherapy and 3 months (D84 ± 5 days) after the start of treatment. Biopsies will be proposed only if disease progression is observed and 50 days after the start of chemotherapy following immunotherapy. Samples will be processed using the standard formalin-fixed paraffin-embedded (FFPE) procedure.

Liquid biopsies will be taken before the start of anti-PD-1 immunotherapy, before and after each of the 4 cycles (20-day cycle) up to 84 days (± 4 days) after the start of immunotherapy, and finally at the end of anti-PD-1 immunotherapy (10 samples per patient). Biopsies will also be performed in the event of disease progression prior to the initiation of a new line of chemotherapy. Liquid biopsies will be collected in anti-coagulant ethylenediaminetetraacetic acid (EDTA)-treated RNA Complete blood collection tubes (BCT). Cell-free plasma samples will be isolated by a two-step centrifugation (1,200 g, 10 min and 16,000 g, 10 min) and aliquoted before storage at -80 °C in the Biobank of the UNICANCER Centre Paul Strauss in Strasbourg.

#### Tumor analysis by spatial transcriptomics and single cell RNA-seq

Spatial transcriptomics will be performed on FFPE tissue sections using the 10X Genomics Visium Spatial Gene Expression platform (10X Genomics, GenomEast, IGBMC, Illkirch, France). Histological sections will be stained using hematoxylin and eosin (H&E) to select the most relevant areas for analysis. Using a Leica RM2235 microtome (Leica, Nanterre, France), tissue sections will be cut from FFPE tissue blocks and placed within the etched frames of the capture areas on the active surface of the Visium Spatial Slide using the Visium CytAssist. The slide will be dried in an oven overnight at 37 °C and then at 60 °C for 25 min before dehydration in ethanol and H&E staining. The slide will finally be transferred to water and mounted in 87% glycerol before image acquisition on the same day. Image mosaic of each section will be acquired to generate a brightfield image of each section including the fiducial marker frame. Subsequently, stained sections will be processed as described in the demonstrated protocol “Visium Spatial Gene-Expression Reagent kits for FFPE, UserGuide” (CG000407). This kit enables spatial quantification of the expression of approximately 18,000 genes on FFPE tissue sections using a pair of specific probes for each targeted gene. Slides containing 4 capture zones will be used. Each 6.5 × 6.5 mm capture zone contains ~ 5,000 spots, and each spot is covered with capture probes bearing a unique barcode, known as a spatial barcode. Quantification and quality control of the final libraries will be performed using Bioanalyzer 2100 (Agilent Technologies, Santa Clara, United States).

Libraries will be sequenced on an Illumina NextSeq 2000 platform as paired-end 28 + 50 bases reads. Sequencing data will be processed using the Space Ranger software (10 × Genomics) for analyzing and visualizing spatial gene data produced by the 10 × Genomics Visium Platform including detection tissue, alignment reads, generation of read counts matrices, clustering and gene expression analysis, and place spots in spatial context on the microscope slide image. Differentially expressed gene (DEG) analysis between responders and non-responders will be performed using pseudo-bulking on DESeq2.

Signaling pathways and cellular/molecular processes characterized by the expression of genes identified in each spot will be identified using online bioinformatics tools (such as Database for Annotation, Visualization and Integrated Discovery (DAVID) and Search Tool for Retrieval of Interacting Genes/Proteins (STRING)).

Single cell RNA-seq analysis will also be performed on the same fixed tissues. Advances in technology have enabled RNA extraction from FFPE which had been a challenge due to RNA modification and degradation [44]. The protocol includes sample selection, paraffin dissolution, single nuclei isolation, and permeabilization, single-strand DNA blocking, reverse transcription for converting the mRNAs into cDNAs labeled with specific barcodes, and sequencing library by adding sequencing adapters and PCR amplification. A trypan blue exclusion assay will be used to determine cell number and viability using a Neubauer Chamber. Cells will be processed using the Chromium iX (10X Genomics). Chromium Single-Cell 3′ Reagent Kits (10X Genomics ref. CG00052) will be used to generate sc-3′ mRNA-seq libraries. Quality control and quantification of libraries will be performed using Bioanalyzer 2100 (Agilent Technologies). Generated libraries will be sequenced on NextSeq 2000 (Illumina, San Diego, United States) sequencer as 28 + 85 bases paired-end reads.

#### Profiling circulating miRNA from liquid biopsies

The miRNAs will be extracted from 200 μl of cell-free plasma using the miRNeasy serum/plasma extraction kit (Qiagen) according to the manufacturer’s instructions. RNA quality will be assessed using a Nanodrop Spectrophotometer (Thermo Scientific), resulting in a mean 260/280 ratio of 1.95. RNA will be processed for miRNA-sequencing and RT-qPCR. The sequencing of miRNAs extracted from the serum through liquid biopsy will be performed by Qiagen, a leading provider for RNA studies. The study will include sample quality control using qPCR, library construction and quality control, miRNA sequencing, and analysis of the results.

As a complement, digital PCR (dPCR) based on the partitioning of the sample into thousands of micro-reactions of defined volume will be performed with miRNA of interest because of higher precision and sensitivity to detect low-abundance miRNAs in plasma samples [45].

The potential predictive value of miRNAs signature will be validated. In addition, optimal expression cutoff values will be determined using receiver operating characteristic (ROC) curve analysis to determine the relationship between miRNAs signature and Overall Response Rate (ORR; used as an endpoint). Hazard ratios will be adjusted in multivariate models including the principal known confounding prognostic factors, such as patient age, tobacco smoking, treatment, co-morbidities, margin status, extra-capsular status, tumour localization, differentiation, stage, lymph node involvement, and tumor size.

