**Methods:**

The IPRICE study is a single-center, prospective, non-randomized, open-label, and interventional clinical trial. Liquid and tumor biopsies will be performed in 54 patients with recurrent/metastatic (R/M) HNSCC undergoing anti-PD-1 immunotherapy alone to compare the evolution of gene expression and immunological profile between responders and non-responders. We will use a multidisciplinary approach including spatial transcriptomics, single seq-RNA analysis, clinical data, and medical images. Genes, pathways, and transcription factors potentially involved in the immune response will also be analyzed, including genes involved in the interferon-gamma (IFN-γ) pathway, immunogenic cell death and mitophagy, hypoxia, circulating miRNA-mediated immunomodulation, cytokines, and immune repertoire within the tumor microenvironment (TME). With a follow-up period of 3-years, these data will help generate effective biomarkers to define optimal therapeutic strategy and new immunomodulatory agents based on a better understanding of primary/secondary resistance mechanisms. Tumor biopsy will be performed initially before the start of immunotherapy at the first tumor assessment and is only proposed at tumor progression. Clinical data will be collected using a dedicated Case Report Form (CRF).

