## Methods/design

### Study design

The IPRICE study is a single-center, prospective, non-randomized, open-label, and interventional clinical trial of patients managed at the Cancer Institute of Strasbourg (ICANS) Europe (Strasbourg). Study inclusion period will be 3 years; each patient will be followed up for 3 years and the total study duration will be 6 years. The study design is depicted in Fig. 1. The IPRICE study and this manuscript have been written in accordance with standard protocol items, namely recommendations for interventional trials (SPIRIT).

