### Study objectives and endpoints

The main objective of this study is to identify effective biomarkers of response to PD-1 checkpoint blockade using combinatorial omics analysis including spatial transcriptomics, scRNA-seq, and miRNomics. The primary endpoint is the prospective validation of the IFN-γ–related gene expression signature to predict response to PD-1 checkpoint blockade (overall response including complete response (CR) and partial response (PR)). Tumor response was defined according to the Response Evaluation Criteria In Solid Tumor (RECIST) criteria. Secondary outcomes are the prospective validation of potential response biomarkers (immunogenic cell death and mitophagy-related markers, expression of hypoxia-related markers, and circulating miRNA-mediated immunomodulation). Exploratory outcome measures will include dynamic and differential profiling of the immune repertoire in the TME between responders and non-responders.

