## Discussion

Immune checkpoint inhibitors of PD-(L)1 represent a significant breakthrough in the treatment of HNSCC in the R/M setting because of the prolonged responses observed with a near doubling of the 2-year survival in the Keynote-048 study. However, response rates remain < 20% with life-threatening progression, even hyperprogression occurring in as much as 30% of the cases in some studies, resulting in excess mortality observed in the initial part of the immunotherapy arms survival curves [46]. The increase of this response rate requires new immunomodulatory agents and the development of effective biomarkers to support a better selection of patients most suitable for immunotherapy. But the last few years have seen a number of failures in clinical drug development for HNSCC, which may reflect an incomplete understanding of the TME including the molecular and cellular drivers of immune escape. In this study, we consider the understanding of the dynamic evolution of TME under immune checkpoint inhibitors to be of crucial importance. This will be accomplished through the emergence of breakthrough technologies including scRNA-seq and spatial transcriptomics (performing a deep analysis with cellular resolution of the main cellular subsets), and the anatomical localization of HNSCC allowing for multiple biopsies during the treatment. However, we realize that the main limitation of this study is the TME heterogeneity. Indeed, a single tumor sample may not be representative of the immune infiltration landscape if, for example, the same tumor has both “immune cold” and “immune hot” regions which could affect up to a third of the patients [26]. Complementary approaches such as liquid biopsy could help overcome this problem, and will be included in this study to focus on the exploration of circulating miRNA-mediated immunomodulation and circulating cytokines.

In this single-center prospective study, we will study biological samples of patients undergoing anti-PD-1 immunotherapy to generate effective biomarkers to define the optimal therapeutic strategy and identify potential new immunomodulatory targets in patients with R/M HNSCC.

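### miRNA cut-offs optimised by ROC in the trial's only described cohort cannot also be validated there: performance at the cut-off will be optimistic

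*Protocol article*

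**What the plan says.** Under Study objectives and endpoints, the protocol article states: "Secondary outcomes are the prospective validation of potential response biomarkers", and it lists circulating miRNA-mediated immunomodulation among them. The section on profiling circulating miRNA repeats the claim: "The potential predictive value of miRNAs signature will be validated". Its next sentence adds that "optimal expression cutoff values will be determined using receiver operating characteristic (ROC) curve analysis", the purpose being "to determine the relationship between miRNAs signature and Overall Response Rate (ORR; used as an endpoint".

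On the source of the measurements, the same section says "RNA will be processed for miRNA-sequencing and RT-qPCR", with digital PCR to follow on miRNAs of interest. It names no signature and no cut-off value.

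On the patients, the abstract says "Liquid and tumor biopsies will be performed in 54 patients with recurrent/metastatic (R/M) HNSCC", and Study design describes a "single-center, prospective, non-randomized, open-label, and interventional clinical trial of patients managed at the Cancer Institute of Strasbourg". No other cohort appears in the article.

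**The concern.** Validation means applying a rule fixed beforehand to patients whose outcomes played no part in making it. Here one part of the rule, the cut-off, is to be derived from response. With only one cohort described, the patients who set the cut-off are also those in whom its performance would be read. A search over all possible cut-offs finds apparent separation even in noise.

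The article is also not consistent about the status of this work. The main objective is to identify biomarkers, with miRNA profiling among the tools, and the Background and Discussion speak of exploring circulating miRNA. The secondary outcome and the miRNA section speak of validation. One cohort cannot both set a cut-off and validate it.

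At stake is how the secondary result is read. Sensitivity and specificity published under the label of prospective validation would be expected to fall in new patients, and the nominal 5% level would not hold at the chosen cut-off.

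**Working it through.** **Plan's own figure.** The article gives no target performance for the miRNA signature, so there is none to reproduce. The 54 patients were sized for the IFN-γ signature; here 54 is only an input.

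**Inputs from the article**
- Cohort: 54 patients, one centre.
- Cut-off: chosen by ROC against overall response.
- Background response: the Discussion says "response rates remain < 20% with life-threatening progression", and the Background gives 23.3% for one pembrolizumab subgroup. 54 × 0.20 = 10.8 and 54 × 0.233 = 12.6, so about 11 to 13 responders.

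**Assumptions, not in the article**
- Responders: 9, 11, 13 and 22 of 54 (17%, 20%, 24%, 41%), to bracket the background rates and test a higher count.
- Optimal means the cut-off that maximises the Youden index.
- The dichotomised marker is compared with response by a two-sided Fisher test.

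**Formula.** J = sensitivity + specificity − 1. For a marker unrelated to response and a cut-off fixed beforehand, the expected proportion of positives is the same in responders and non-responders, so expected J = 0. The ROC-optimal cut-off instead takes the largest J over all 53 possible splits of 54 ordered patients, and that maximum lies above 0 by construction.

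**Simulation of a useless marker** (20,000 runs per row; cut-off and performance taken in the same patients)

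| Responders of 54 | Apparent sensitivity | Apparent specificity | Apparent J | p ≤ 0.05, direction free | p ≤ 0.05, direction fixed | p ≤ 0.05, cut-off fixed at median |
|---|---|---|---|---|---|---|
| 9 | 0.69 | 0.60 | 0.29 | 24% | 12% | 2.5% |
| 11 | 0.67 | 0.60 | 0.27 | 27% | 14% | 4.1% |
| 13 | 0.66 | 0.59 | 0.26 | 25% | 13% | 0.8% |
| 22 | 0.62 | 0.60 | 0.22 | 25% | 13% | 1.3% |

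Sensitivity and specificity are for the free-direction search. For 11 responders, 0.669 + 0.604 − 1 = 0.273. The simulation error on a rate near 25% is √(0.25 × 0.75 / 20,000) = 0.003. With the direction fixed, apparent J is 0.16 to 0.21.

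The last column is the control. With the cut-off fixed beforehand, the same test stays below 5%, so the excess comes from the search.

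The result is not sensitive to the responder count. Even at 32 responders (54 × 0.60 = 32.4, as if the 60% expected in signature-positive patients applied to everyone), J is 0.22 and p ≤ 0.05 occurs in 24% of runs.

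**If miRNAs are also selected on these outcomes** (11 responders, 3,000 runs, independent useless candidates; the candidate counts are assumed), the best of 5, 10 or 50 shows J of 0.38, 0.42 or 0.51, with p ≤ 0.05 in 73%, 92% or 100% of runs.

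**Stated safeguards.** The adjusted p-value under Statistical analysis belongs to the DESeq2 expression analysis, not to the ROC cut-offs. The multivariable adjustment in the miRNA section addresses confounding; it does not undo the cut-off search.

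**The case against.** The strongest reply is that this is a condensed article. Cross-validation, bootstrap correction and a working definition of validation are commonly left to the full protocol or analysis plan, which are not shown. That stands: a reader might infer that no internal correction is planned, and the article does not show that. What the article does state is a cut-off derived from response beside the word validation, with one cohort described. Resampling set out elsewhere would correct the estimates, but the result would still be internal validation.

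Second, several links are inferred. The article does not say that the miRNAs will be selected in this cohort; sequencing may be only the means of measurement, and the signature may be fixed beforehand. It names no optimality criterion and no test at the cut-off. The cut-off step is introduced as an addition to the validation step, so the two may be separate. All of this stands. It is why the multi-candidate figures are illustrations and the single-marker figures rest on labelled assumptions. It also limits the scope: the AUC of one pre-specified score is not biased by the choice of cut-off.

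Third, a reader might infer that a false miRNA marker will probably be declared validated. The documents do not support that. The single-marker rate is about one in four, or about one in eight with the direction fixed, and the article gives no criterion for declaring validation. Higher rates need candidate counts that it does not supply.

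Finally, this is one of several secondary outcomes, and the article elsewhere speaks of potential biomarkers. That lowers the severity but does not remove the point.

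**Conclusion.** The concern holds for performance at the cut-off and for the label. If the stated rule is followed in the only cohort described, sensitivity, specificity and any p-value at the chosen cut-off will be optimistic. The AUC will be too, but only if the signature is also selected here.

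For a useless single marker the apparent Youden index is 0.22 to 0.29 instead of 0, and p ≤ 0.05 occurs in about 24 to 27% of trials (12 to 14% with the direction fixed). These sizes assume a Youden-optimal cut-off, a Fisher test and 9 to 22 responders. The direction of the bias needs none of these assumptions. The inflation grows with selection among candidates, for example to a Youden index of about 0.42 for 10 independent useless miRNAs, an assumed number.

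This should be fixed, but it concerns a secondary outcome. The primary IFN-γ endpoint and the sample size of 54 do not depend on it.

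**What to change.** - **Label.** In Study objectives and endpoints and in the miRNA section, call signatures and cut-offs derived in this cohort development or internal validation. Keep validation for signatures and cut-offs locked before outcomes are seen.
- **Main measure.** Report the AUC of the continuous score with a 95% CI. If miRNAs are selected in this cohort, correct the AUC for optimism as well.
- **Cut-off performance.** Report sensitivity and specificity only after bootstrap or cross-validated optimism correction, with any miRNA selection and the cut-off choice repeated inside each resample.
- **p-value.** Use one that allows for the cut-off search, by permutation of the whole procedure or a maximally selected statistic.

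If the analysis plan already contains these steps, only the label needs to change. The cost is extra analysis code and a less favourable claim; no new patients or samples are needed. The change is best made before outcome data are analysed.

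### The miRNA analysis specifies adjusted hazard ratios without defining a time-to-event endpoint, and lists at least 11 adjustment factors for 54 patients

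*Protocol article*

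**What the plan says.** The section of the protocol article on profiling circulating miRNA describes two steps. First, ROC analysis is to find expression cutoffs "to determine the relationship between miRNAs signature and Overall Response Rate (ORR; used as an endpoint"). Second, the next sentence says that "Hazard ratios will be adjusted in multivariate models including the principal known confounding prognostic factors". The list of factors is then given by way of example: "such as patient age, tobacco smoking, treatment, co-morbidities, margin status, extra-capsular status, tumour localization, differentiation, stage, lymph node involvement, and tumor size". That sentence names no endpoint of its own.

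Under study objectives and endpoints, response means complete or partial response by RECIST. Circulating miRNA appears there among the secondary outcomes, as a potential biomarker of response. Neither that section nor the statistical analysis section defines progression-free survival, overall survival or duration of response as an outcome of this study. Survival figures appear only when earlier studies are described.

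On size, the abstract says that "Liquid and tumor biopsies will be performed in 54 patients". On response, the discussion says that "response rates remain < 20% with life-threatening progression", and the background gives an objective response rate of 23.3% for pembrolizumab alone in patients with CPS of 20 or more. The statistical section expects 60%, but only in patients with the IFN-γ signature.

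**The concern.** Two things do not fit.

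The first is the effect measure. A hazard ratio compares event rates over time and needs an outcome with a time origin, an event and a censoring rule. Response is recorded here as yes or no. A reader cannot tell whether the adjusted analysis concerns response, and should give odds ratios, or a survival outcome that has not been named. The article chose to state the measure, so this is a mismatch in the text and not a detail deferred to an analysis plan.

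The second is the number of factors. The information in such a model is set by the number of responders or events, and 54 patients supply few of either. Fitting 12 or more terms to so few outcomes gives wide, unstable estimates that tend to lie too far from no effect. The article says that the predictive value of the signature will be validated, so an adjusted association swollen by overfitting could be read as confirmation.

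A smaller point concerns "margin status, extra-capsular status, tumour localization, differentiation, stage, lymph node involvement, and tumor size". Margin status and extra-capsular status exist only for patients with a surgical specimen, while the study enrols "adult patients diagnosed with R/M HNSCC considered incurable by local therapies". Patients who had no surgery will have no value for these two factors.

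**Working it through.** **The plan's own figure.** The document gives no expected number of responders or events for this model, so there is no such figure to reproduce. The total of 54 cannot be rebuilt either, because no comparison rate or exclusion rate is given. The point does not depend on how 54 was reached.

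**Inputs from the protocol article.**
- N = 54 (abstract, methods). The statistical section says this already allows for exclusions, so the number analysed may be smaller.
- Response rate: below 20% (discussion), taken here as 20%, its upper limit; 23.3% for CPS of 20 or more (background).
- Named factors: age, smoking, treatment, co-morbidities, margin status, extra-capsular status, localization, differentiation, stage, lymph nodes, tumor size = 11.
- Terms: 11 + 1 for the signature = 12. This is a minimum: the list is open-ended, and a factor with more than two categories needs more than one term.

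**Assumptions not in the document.**
- Favourable response case: half the patients carry the IFN-γ signature and respond at 60%, the others at 20%. Overall rate = 0.5 × 0.60 + 0.5 × 0.20 = 0.40.
- Survival reading: 60% to 90% of patients have an event during follow-up.

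**Formula.** Outcomes per term = (54 × proportion with the outcome) / 12.

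| Reading | Proportion | Responders or events | Per term |
|---|---|---|---|
| Response, general figure | 20% | 10.8 | 0.90 |
| Response, CPS of 20 or more | 23.3% | 12.6 | 1.05 |
| Response, favourable (assumed) | 40% | 21.6 | 1.8 |
| Survival, low (assumed) | 60% | 32.4 | 2.7 |
| Survival, high (assumed) | 90% | 48.6 | 4.1 |

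The 60% row also covers the extreme case in which the rate expected for signature-positive patients applied to everyone: 32.4 responders, 2.7 per term.

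**What this does to a model.** Logistic models were fitted to simulated data for 54 patients in which no predictor was related to response.
- With 11 responders and 12 predictors, the mean apparent AUC was 0.83, against a true value of 0.50. With 2 predictors it was 0.62.
- With 22 responders and 12 predictors it was 0.78.
- With 11 responders and 12 predictors, one given noise predictor showed an adjusted odds ratio above 2 or below 0.5 per standard deviation in 27% to 29% of fits. With 2 predictors the share was 8% to 9%.
- Complete separation, where estimates diverge, was uncommon: 0% to 7% of fits at response rates of 20% to 23.3%.

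The main harm is thus exaggeration of estimates, with outright failure of the fit the exception.

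**A short list.** The signature plus one covariate gives 10.8 / 2 = 5.4 responders per term at 20%. The signature plus two gives 10.8 / 3 = 3.6. That is still thin, which is why penalisation is advisable as well as a short list.

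**The case against.** The strongest reply is that the hazard-ratio sentence stands apart from the ROC sentence, and that survival may have been meant. Patients are followed for 3 years, the factors are called prognostic, and the sample-size paragraph mentions censoring. A reader might infer that the plan asks for a hazard ratio of response, but the text does not literally say so. What stands is narrower: response is the only endpoint named for this analysis, and no time-to-event endpoint is defined to which the hazard ratios could belong. The survival reading also does not cure the length of the list, at 2.7 to 4.1 events per term.

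It is also fair that the text speaks of models in the plural and gives the factors as examples. It does not say that all 11 enter one model, and selection or penalisation may be set out in an analysis plan that is not shown. The counts above apply to a model that contains them all.

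A reader might further infer that the model must have more parameters than responders. That fails at 23.3%, where 12.6 responders meet 12 terms, unless multi-level factors or the intercept are counted.

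Nor would the adjusted result be worthless. In a null simulation with 12 noise predictors, a nominal 5% test of one coefficient was falsely positive in 6% (Wald) to 11% (likelihood ratio) of logistic fits with 11 responders, and in about 9% of Cox fits with 32 or 49 events. That inflation is real but moderate. The apparent AUC describes the whole model, whereas the article applies ROC analysis to the signature, so the AUC shows overfitting in general and not the error in the signature's own estimate.

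Last, the document gives no share of patients without a surgical specimen, and incurable disease does not exclude earlier surgery. The loss of patients from missing margin or extra-capsular values cannot be sized.

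**Conclusion.** The concern holds in two parts. The adjusted hazard ratios fit no endpoint that the document defines; this follows from the text alone. The named list is too long for 54 patients on each reading examined: about 0.9 to 1.05 responders per term at the document's response rates, 1.8 at an assumed 40%, and 2.7 to 4.1 events per term for survival at assumed event shares of 60% to 90%. These figures rest on one model holding all 11 factors and a signature entered as a single term. More levels, more factors or fewer analysed patients would lower them; fewer factors would raise them.

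The evidence for exaggerated estimates is clearest for response. For survival the shortage is milder, but it remains. The matter concerns a secondary biomarker outcome and leaves the primary endpoint and the sample size untouched.

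**What to change.** State which outcome the adjusted miRNA analysis concerns.

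- **If response:** replace hazard ratios with odds ratios from a logistic model, preferably penalised (Firth's method is one option). Include the signature and only one or two baseline covariates, named before the outcome data are analysed. Report the other factors descriptively.
- **If progression-free or overall survival:** define that endpoint, with its time origin, event and censoring rule. Use a Cox model only there, with a similarly short covariate list.
- **In both cases:** leave margin status and extra-capsular status out of the model, since they exist only for patients with a surgical specimen.

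The cost is a change of wording in the protocol and analysis plan; no new data are needed. The price is that fewer confounders are adjusted for at once, so some confounding of the signature's effect may remain and should be acknowledged when the result is reported.
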